### Outcomes

The primary outcome will be the onset muscular contraction of the four core muscle groups during the Abdominal Drawing in Maneouver (ADIM), Contralateral Arm Lift (CAL), Valsalva maneuver, and voluntary contraction of the PF, in sitting and standing positions:

Onset muscular contraction of the three muscles that conform the Lateral Abdominal Wall (LAW); Transversus abdominis (TrA), Internal oblique (IO), External oblique (EO).Onset muscular contraction of Lumbar Multifidus (LM).Onset excursion of the Diaphragm (DPH).Onset excursion of the Pelvic Floor (PF).

The secondary outcomes are; the percentage of change in muscle thickness in the LM and LAW (IO,EO,TrA) represented as average contraction thickness (cm)–average thickness at rest (cm) / average thickness at rest (cm)*100 [12]; the excursion of the DPH [15] and the excursion of the bladder trough the contraction of the PF muscles [16]. Finally, the degree of disability through the Oswestry disability questionnaire) [17].

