For the analysis of the differences between the groups in the continuous quantitative dependent variables that meet the assumption of normality, a mixed 4-by-2-by-2 covariance analysis (ANCOVA) will be used, with the maneuver (ADIM, CAL, Valsalva, voluntary PF contraction) and the position (sitting, standing) as intra-subject factors, the group (pain, healthy) as an inter-subject factor, and the BMI (Body Mass Index) as a covariant. The association between abdominal muscle thicknesses with gender, age, and BMI was examined using Pearson’s correlation coefficient and multiple regression analysis. Compliance with the assumption of sphericity will be assessed with the Mauchly test and that of equality of covariance matrices with the Box test. The partial eta-square coefficient (p2) will be used as an estimator of the size of the ANCOVA main effects and interactions.

It will be performed the Kruskal-Wallis H test for analyze the differences between independent variables (cases and controls) and the onset muscular contraction, as a qualitative ordinal dependent variable. On the other hand, the t-Student test for independent samples with Bonferroni correction will be used for the analysis of post-hoc pairwise comparisons. Cohen’s d (d = 2t / √g) will be used as estimator of the effect size of the post hoc comparisons [31].

If any continuous quantitative dependent variable does not meet the assumptions for carrying out the ANCOVAs, robust analogous methods will be used that do not require compliance with those assumptions, following the procedures described by Wilcox [31]

All analyses will be carried out with the software R Version 4.1.0 (R Core Team (2021). R: A language and environment for statistical computing. R Foundation for Statistical Computing, Vienna, Austria. URL https://www.R-project.org/). An α level of 0.05 with 95% confidence intervals (CI) will be assumed for all analyses.

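### The primary onset outcome spans up to 48 case-control comparisons, none is named as primary, and no multiplicity adjustment is stated for the test assigned to it

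*Protocol article*

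**What the plan says.** The Outcomes section of the protocol article defines a single primary outcome: "The primary outcome will be the onset muscular contraction of the four core muscle groups". It is recorded in four maneuvers (ADIM, CAL, Valsalva, voluntary pelvic floor contraction), each sitting and standing. The list that follows splits the lateral abdominal wall into transversus abdominis, internal oblique and external oblique, and adds lumbar multifidus, diaphragm and pelvic floor. That makes six structures in what the article calls four muscle groups. No structure, maneuver, position or summary across them is singled out.

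The Statistical analysis section has two analysis routes:

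- Continuous dependent variables go into a mixed ANCOVA with maneuver and position as within-subject factors and group as the between-subject factor.
- A Kruskal-Wallis test compares cases and controls "and the onset muscular contraction, as a qualitative ordinal dependent variable".

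The next sentence introduces a Student t-test "with Bonferroni correction will be used for the analysis of post-hoc pairwise comparisons". The section closes with "An α level of 0.05 with 95% confidence intervals (CI) will be assumed for all analyses".

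The Sample size calculation section bases the 82 subjects on the between-subject factor of a mixed 4-by-2 ANOVA, with effect size 0.25, correlation 0.50, power 80% and a level of 0.05.

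**The concern.** The main objective is whether simultaneous contraction of the core muscles differs between people with non-specific low back pain and healthy subjects. As written, many separate onset results could each answer that question, and the plan does not say in advance which one does. A significant difference in one muscle, in one maneuver and one position, could be reported as a positive primary result although it was one of dozens examined.

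Neither of the two possible safeguards clearly reaches onset. The ANCOVA would combine maneuvers and positions in one model, but it is reserved for continuous variables and onset is declared ordinal. The Bonferroni correction belongs to post-hoc t-tests. With only two groups, a Kruskal-Wallis test leaves no pairwise group comparison to follow up, and a t-test is not the natural follow-up for an ordinal variable.

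**Working it through.** **Inputs.** From Outcomes: 6 structures (4 if the abdominal wall counts as one), 4 maneuvers, 2 positions. From Statistical analysis: level 0.05. From Sample size calculation: f = 0.25, correlation 0.50, power 80%, N = 82. From the Abstract: 41 per group. The article gives no correlation between structures, so the correlation patterns below are assumptions.

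**1. The plan's own figure.** For the between-subject effect with m = 4 repeated measures, lambda = f² x N x m / (1 + (m - 1) x rho). At N = 82 this is 0.0625 x 82 x 4 / 2.5 = 8.2, with 1 and 80 degrees of freedom, and power is 80.8%. At N = 80 it is 79.8%. The stated 82 therefore reproduces, as the size for one test at 0.05. For a single cell (m = 1) with the same f, 80% power would need 128 subjects even without adjustment.

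**2. Number of comparisons.** 6 x 4 x 2 = 48 cells, or 4 x 4 x 2 = 32 if the abdominal wall is one group. Kruskal-Wallis takes no within-subject factor, so one test per cell is the natural reading. One test per structure would be 6 tests.

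**3. Familywise error with no true difference, each test at 0.05.** Under independence this is 1 - 0.95^K. The equicorrelated columns assume the same correlation between all test statistics and use numerical integration of a normal model.

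| Tests (K) | Independent | Equicorrelation 0.3 | Equicorrelation 0.5 | Equicorrelation 0.8 |
|---|---|---|---|---|
| 48 | 91.5% | 79% | 61% | 30% |
| 32 | 80.6% | 68% | 52% | 26% |
| 6 | 26.5% | 24% | 21% | 14% |

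The expected number of false positives among 48 tests is 48 x 0.05 = 2.4, whatever the correlation.

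**4. A different dependence pattern.** This simulation ran 48 Kruskal-Wallis tests, 41 against 41, with correlation only between conditions within the same structure (4000 runs). The familywise error was 88% at 0.3, 83% at 0.5, 73-75% at 0.7 and 56-60% at 0.9.

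**5. Pooling the eight conditions into one test per structure.** This ignores that each person contributes eight correlated values. The variance of the group contrast is inflated by 1 + 7 x rho. At rho = 0.5 that is 4.5, so the critical value 1.96 acts like 1.96 / √4.5 = 0.92, and the error of one test is about 35%. Simulation gave 27%, 35% and 45% at correlations of 0.3, 0.5 and 0.8.

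**6. With adjustment.** Bonferroni over 48 uses 0.05 / 48 = 0.00104. The familywise error is then 4.9% under independence and 3.2% at equicorrelation 0.5.

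**The case against.** The article never says that 48 tests will be run. It gives one sentence on the Kruskal-Wallis test, without a count and without saying whether structures or conditions are combined. It speaks of four muscle groups, so 32 tests, or four to six pooled ones, can also be read from it. The Bonferroni sentence directly follows the Kruskal-Wallis sentence, and its family is open, so cell-level onset contrasts might be meant to fall under it. A condensed article may also leave the definition of families to an analysis plan that is not shown.

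Much of this stands against a stronger reading. A reader might infer that 48 separate tests are planned, each unadjusted at 0.05, and that a false positive is therefore nearly certain. The documents do not support that: the count is inferred, the reach of the Bonferroni correction is ambiguous, and 91.5% requires independence. These are repeated measures on the same people, and the sample size itself assumes a correlation of 0.50.

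The objection does not remove the point. The article does more than leave detail out: it fixes the primary test, the level for all analyses and the place where the correction applies, and as written these leave the onset family without stated protection. Fewer tests reduce the inflation but do not bring it to 5%, and pooling conditions in a Kruskal-Wallis test creates a further error.

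**Conclusion.** The point holds in limited form. The primary outcome covers up to 48 case-control comparisons, none is designated primary, and no adjustment is stated for the Kruskal-Wallis tests assigned to onset. If every cell is tested at 0.05, the familywise error is about 60-90% for correlations up to 0.5, with 91.5% as the figure under independence and about 30% at equicorrelation 0.8. With one valid test per structure it is about 21-26% at correlations up to 0.5. These figures assume no true difference anywhere, no adjustment, and illustrative correlation patterns. The size therefore depends on a test count and a dependence that the article does not give, but every scenario examined is well above 5%.

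**What to change.** Before analysis, choose one of two routes and write it into the plan.

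- **Preferred.** Designate one primary onset comparison at 0.05. The natural candidate is the between-group effect for which the study was sized. Estimate it with a method that suits an ordinal outcome and respects the repeated measures within a person. Label the structure-, maneuver- and position-specific onset contrasts as secondary.
- **Alternative.** Keep the individual onset comparisons as primary, state how many there are, and apply Holm or Bonferroni explicitly across the whole family.

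In either case, say which comparisons the existing Bonferroni sentence covers. The primary test should not be a new summary endpoint that the article does not define. Nor should it be a group-by-muscle interaction, because the sample size was not set for one.

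This changes the analysis text only and needs no new data. The cost is stricter thresholds for individual contrasts (0.00104 for a Bonferroni correction over 48). The sample size was set for a single ANOVA effect at 0.05, so the stated 80% power does not extend to the adjusted contrasts, and it is only a guide for an ordinal method.
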